**Fig. 1 Fig1:**
[figure not shown]
HYDRA study design: two parallel, noncomparative, open label phase-I trials. Randomization is performed for translational research purposes. ^*^ Radiotherapy with/without concurrent radiosensitizer. Oropharyngeal and hypopharyngeal carcinoma are amenable for inclusion. Laryngeal carcinomas are initially excluded until these patients are also considered eligible after interim analysis. Abbreviations: BL: baseline. LD: last day of treatment. SOC: standard of care. HNSCC: head and neck squamous cell carcinoma. MBI: model-based indication for proton therapy, according to the Dutch model-based selection criteria. R: randomization by minimization based on HPV status (positive vs. negative), stage (I-II vs. III-IV), and concurrent radiosensitization (yes vs. no)

### Study participants

Patients with histology-proven squamous cell carcinoma of the oropharynx and hypopharynx, who are eligible for curative intent proton or photon therapy (with or without concurrent radiosensitizer) are amenable for inclusion. Patients must be 18 years or older and have WHO performance status of 0–2. Patients with laryngeal carcinoma are initially excluded until these patients are also considered eligible for treatment with HYDRA as described in the safety and statistics section. The main exclusion criteria are previous irradiation, chronic inflammatory disease or immune disorder and other malignant disease within the last two years.

### Interventions

#### HYDRA

The HYDRA dose prescriptions are delivered in 20 fractions. Gross tumor volume (GTV) is determined by the combination of PET-CT/MRI and ultrasound. The prescriptions consist of a focal inhomogeneous boost to the GTV of both the primary tumor and the pathological lymph nodes (CTV_5900 = GTV − 3 mm), a “conventional” simultaneous integrated boost (SIB) on the clinical target volume (CTV) of 55 Gy (CTV_5500 = GTV + 5 mm) and elective field radiotherapy of 40 Gy (CTV_4000 = GTV + 10 mm + elective lymph nodes). Delineations are in accordance with Grégoire et al. [21] and Biau et al. [22]. For the 55Gy and 40Gy CTVs, a 3 mm setup and 3%-range robustness is applied in case the patient is treated with proton therapy or a planning target volume (PTV) expansion margin of 3 mm is applied for photon radiotherapy. Target coverage is evaluated according to standard of care (D98 > 94% in voxel-wise minimum plan for protons, and D98 > 95% of the PTVs for photons [23]).

The focal boost to the GTV is delivered with a mean dose of 59 Gy and a maximum dose of 63.13 Gy (107% of 59 Gy). No more than 2% of the GTV should receive more than 63.13 Gy. The mean dose of 59 Gy corresponds to an equal late normal tissue toxicity probability after conventionally fractionated radiotherapy of 70 Gy in 35 fractions, considering an α/β = 3 for normal tissue. A 3 mm contraction margin is created to ensure that the 59 Gy boost always lies within the GTV (analogous to a negative PTV). If, after this step, there is no GTV_5900 volume left in the case of small tumor bulk, only a CTV_5500 boost will be prescribed. The mean dose of 59 Gy is a soft constraint: it is preferable but not obligatory and may be lower, depending on the 55 Gy boost dose constraints to the CTV.

The boost on the CTV has a mean dose of 55 Gy with an inhomogeneous distribution between 52.5 Gy at the border (95% of 55 Gy) and a maximum dose of 63.13 Gy within the GTV (107% of 59 Gy). No more than 2% of the CTV_5500 minus the GTV_5900 should receive more than 58.85 Gy (107% of 55 Gy). The volume that receives > 58.85 Gy should ideally be within the GTV_5900, but it is mandatory that this does not lie outside the CTV_5500. Discontinuation and treatment modification strategies are in accordance with the standard of care.

#### Standard of care (SOC)

Standard of care dose prescriptions consist of an elective dose of 54.25 Gy and a simultaneous integrated boost of 70 Gy to the primary tumor and pathologic lymph nodes in 35 fractions, five or six fractions per week.

#### Concomitant systemic therapy

Patients who receive HYDRA, as well as patients who receive standard of care treatment, may require the addition of a concurrent radiosensitizer based on clinicopathological features according to the standard of care.

### Safety, interim analysis and statistics

While there are reports about acceptable acute toxicity following hypofractionated chemoradiotherapy in advanced stage HNSCC [24–26], concerns about late toxicity remain, especially for laryngeal carcinoma. Therefore, an independent Data Safety Monitoring Board (DSMB) is established to perform ongoing safety surveillance and planned interim analyses for HYDRA-protons and HYDRA-photons independently.

After the tenth included patient has reached six months of follow-up, the DSMB will be consulted on whether to terminate the study, continue or expand the inclusion criteria with tumors originating from the larynx. Toxicity after six months is considered a preliminary surrogate for late-onset toxicity. Accrual will not be interrupted until the tenth patient has reached six months of follow-up, so at the time of interim analysis we expect that approximately 15 patients per treatment arm will be included, under the assumption that accrual will be linear. However, only the first ten patients with a follow-up of 6 months will be evaluated.

This decision for trial continuation is based on the number of patients who experience dose limiting toxicities (DLTs). A DLT is defined as grade 3–4 toxicity > 6 months after radiotherapy. Grade 3–4 toxicity should be considered causally related to radiotherapy, i.e. in addition to symptoms/increased severity than already present at baseline. The prevalence of DLTs is conventionally determined to be 33% for phase-I trials with a recommended acceptable dose for phase-II just below this toxic dose level [27]. This is in line with data derived from a phase-III trial evaluating standard of care chemoradiotherapy for oropharyngeal carcinoma [28]. At six months follow-up (− 6 to + 8 weeks), 13% of patients had grade 3–4 toxicity, and 17% was tube-feeding dependent [9]. Therefore, an additional expansion cohort of ten patients can be included (up to a total number of 25 included patients in total per treatment arm) if 3 or fewer patients experience grade 3–4 toxicity at six months after radiotherapy. If up to one patient experiences grade 3–4 toxicity after six months, laryngeal carcinoma patients may also be included. If more than three patients have grade 3–4 toxicity, the study must be prematurely ended.

In addition to the interim analysis criteria, the trial will be terminated prematurely in case one of the following stopping rules: one patient with radiotherapy-related death; more than two patients with radiotherapy-related grade 4 toxicity (i.e. an indication for operative intervention because of osteoradionecrosis, ulcer/fistula or bleeding); or more than four patients with radiotherapy-related tube-feeding dependency for more than six months.

For definitive conclusions regarding safety, late toxicity will be determined one year after the last patient has completed HYDRA. This will result in a median follow-up of approximately two years. In the phase-III trial by Gillison et al., there were 10% late grade 3–4 toxicities at one year after treatment [28]. At the final analysis, in case there are five patients (i.e. ≥20% of 25 included patients) experiencing grade 3–4 late toxicities after one year, HYDRA will be considered not feasible.

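### The limit of more than three DLTs is applied only at the interim and accrual is said to run until then, although a fourth DLT among the first nine HYDRA patients already fixes the result

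*Protocol article*

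**What the plan says.** All the relevant text is in the Protocol article, section Safety, interim analysis and statistics.

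- **Timing of the look:** "After the tenth included patient has reached six months of follow-up, the DSMB will be consulted" on whether to end, continue or widen the trial.
- **Accrual before the look:** "Accrual will not be interrupted until the tenth patient has reached six months of follow-up". For that reason "we expect that approximately 15 patients per treatment arm will be included, under the assumption that accrual will be linear", although "only the first ten patients with a follow-up of 6 months will be evaluated".
- **The limit:** expansion is allowed "if 3 or fewer patients experience grade 3–4 toxicity at six months after radiotherapy". Above that, "If more than three patients have grade 3–4 toxicity, the study must be prematurely ended".
- **The event counted:** "A DLT is defined as grade 3–4 toxicity > 6 months after radiotherapy", and it must be attributable to radiotherapy, over and above what was present at baseline.
- **Other safeguards:** an independent DSMB carries out continuing safety surveillance as well as the planned interims, separately for each HYDRA cohort. Further rules end the trial early for one radiotherapy-related death, more than two radiotherapy-related grade 4 toxicities, or more than four patients who depend on tube feeding for over six months. The article introduces these as additional to the criteria of the interim analysis.

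**The concern.** A DLT count can only rise. Once four of the first ten patients in a HYDRA arm have a DLT, the interim can have only one outcome, whatever the remaining patients show. The first ten do not read out together, so this can be known well before the tenth patient's six-month point. The text nevertheless places the limit at that point and says accrual continues up to it.

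Followed as written, patients could go on being randomized to HYDRA, and to its SOC partner, after the plan's own limit has been passed. The Sample size section gives keeping the number of patients at risk low as one reason for the chosen size, so this exposure runs against a stated design aim.

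**Working it through.** **Plan's own figure.** About 15 per arm at the interim plus an expansion of 10 gives 15 + 10 = 25 per arm, as stated.

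**Accrual rate (derived).** With linear accrual and 15 included when patient 10 reads out, 5 patients enter during the read-out lag. For a lag of 6 months from inclusion (assumed), the rate is 5/6 = 0.83 per month, or one patient per 1.2 months. Patient 10 then enters at month 12 and the interim falls at month 18.

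**When the result is fixed.** Let patient k (k = 4 to 10) be the one whose read-out brings the fourth DLT. At that moment k + 5 patients are included, against 15 at the interim. So 15 − (k + 5) = 10 − k more patients enter the HYDRA arm, over (10 − k) × 1.2 months. The extreme is k = 4: month 10.8, 9 included, and 6 more over 7.2 months.

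**Probability.** With independent DLTs at true rate p, P(fourth DLT at patient k) = C(k−1, 3) · p⁴ · (1−p)^(k−4). At p = 0.33, the article's toxic level ("The prevalence of DLTs is conventionally determined to be 33% for phase-I trials"):

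| k | P(k) | 10 − k | product |
|---|---|---|---|
| 4 | 0.0119 | 6 | 0.071 |
| 5 | 0.0318 | 5 | 0.159 |
| 6 | 0.0532 | 4 | 0.213 |
| 7 | 0.0713 | 3 | 0.214 |
| 8 | 0.0836 | 2 | 0.167 |
| 9 | 0.0897 | 1 | 0.090 |
| 10 | 0.0901 | 0 | 0 |
| Sum | 0.432 | | 0.914 |

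The mean number of further HYDRA patients is 0.914 over all arms, and 0.914/0.432 = 2.1 given that the arm stops (2.1 × 1.2 ≈ 2.5 months).

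**Other rates.** The article's reference rate for grade 3–4 toxicity at six months is 13%. The 20% and 50% rows are illustrative.

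| True rate | P(4 or more of 10) | P(fixed before patient 10) | Share of stops fixed early | Mean further patients, all arms | Mean given stop |
|---|---|---|---|---|---|
| 13% | 3.1% | 2.1% | 67% | 0.05 | 1.5 |
| 20% | 12.1% | 8.6% | 71% | 0.20 | 1.7 |
| 33% | 43.2% | 34.2% | 79% | 0.91 | 2.1 |
| 50% | 82.8% | 74.6% | 90% | 2.5 | 3.0 |

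**Error rates.** A fourth DLT at some k ≤ 10 is the same event as 4 or more DLTs in 10. The chance of ending an arm is therefore identical whether the limit acts at once or at the tenth read-out.

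**Sensitivity to the lag.** DLTs are defined from the end of radiotherapy and HYDRA takes four weeks, so a lag of about 7 months is also plausible. The rate is then 5/7 = 0.71 per month, the interim falls at month 21, and the maximum gap is 6 × 1.4 = 8.4 months. The patient counts do not change, because the rate is set by the 15 expected at the interim.

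**Do the other rules cover it?** Four grade 3 DLTs involve no death and no grade 4 event. Even if all four were prolonged tube dependency, the rule for that requires more than four. So four grade 3 DLTs need not trigger any running rule.

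**The case against.** A reader might infer that the protocol forbids any halt to accrual before the interim. The text does not support that. The accrual sentence mainly explains that recruitment is not paused while follow-up matures, and hence why about 15 rather than 10 will be included. The running rules can end the trial at any time, and the DSMB has a continuing remit. The sentence that makes ending mandatory carries no time limit of its own and could be read as acting as soon as the count is reached. The source is also a condensed article, and a DSMB charter may say when the board meets outside scheduled looks.

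The size can be overstated too. The figure of 2.1 patients is conditional on stopping, and the maximum of 6 requires DLTs in all of the first four patients. Some DLTs would be grade 4 or prolonged tube dependency and could end the trial sooner under the other rules. DLTs that surface later than six months, or whose attribution takes time, shorten the gap.

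All of this limits the point but does not remove it. The article sets the other rules apart from the interim's criteria, which places the limit of more than three with the interim. A general surveillance remit is not a trigger. Nor is this only missing detail: the accrual sentence, as printed, points towards continuing.

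**Conclusion.** The point holds as an unreconciled gap between the uninterrupted-accrual sentence and the limit of more than three, not as a ban on stopping early. Up to 6 further patients over 7.2 months could enter a HYDRA arm whose interim result is already decided, and about as many its SOC partner under 1:1 randomization. At a true rate of 33% the mean is 2.1 HYDRA patients given stopping and 0.9 over all arms. At 13% it is 0.05 over all arms, so the gap matters only if HYDRA is in fact toxic, which is the case a stopping rule is written for.

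These figures rest on linear accrual at the plan's implied pace, read-out six months after inclusion in order of entry, and independent DLTs. They are upper limits, because another rule may act first and DLTs may surface later. The change is worth making because it costs almost nothing and leaves the interim's operating characteristics as they are.

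**What to change.** Reconcile the two sentences:

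- State that the plan's existing limit of more than three applies once a fourth radiotherapy-attributed DLT is confirmed among the first ten patients of a HYDRA arm. The DSMB then reviews at once, and further randomization in that HYDRA/SOC pair is held rather than continued until the tenth patient's six-month point.
- Begin the accrual sentence with *Unless this limit has been reached,*.

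The threshold and the mandatory ending stay as the plan has them. Naming the pair settles what happens to the SOC arm, and requiring confirmed attribution respects the plan's own DLT definition.

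The cost is a short amendment, plus reporting of DLTs to the DSMB as they are confirmed, which fits the surveillance already planned. It needs no additional patients, and the chance of ending an arm stays at 43.2% for a true rate of 33% and 3.1% for 13%.

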### Sample size

The stepwise cohort expansion as described above will result in 25 patients per treatment arm. As this is a phase-I trial evaluating HYDRA for multiple tumor subsites and stages with limited patients per treatment group, we anticipate significant heterogeneity. Although this is generally acceptable for a phase-I trial, it should be considered when comparing the immune effects of HYDRA with the standard of care. The immune profile analyses (according to earlier publications [29–31]) in this trial are exploratory in nature and the effect size in this treatment setting is currently unknown. Pragmatically, a number of 25 patients per treatment group is considered a good balance between (1) adequate evaluation of late toxicity, (2) limiting the number of patients at risk and (3) enough patients for exploratory immunological comparisons between treatment cohorts.

Third, both intensity-modulated and image-guided radiotherapy (IMRT and IGRT, respectively) have been the standard of care for almost twenty years now, and have led to significant irradiation volume reduction without compromising clinical outcome [14]. Analysis of IMRT treatment reveals that recurrences are predominantly within the high dose target areas [34]. Optimizing local control without increasing toxicity can thus be achieved by redistributing the radiation dose, creating an inhomogeneous dose distribution towards the most (FDG-avid) active part of the tumor, instead of a conventional homogenous dose distribution with a 1 cm margin around the tumor area. This concept has formed the basis for the ARTFORCE trial, for which data are to be expected within the coming year [15]. As the dose directly outside the tumor is not increased, tumor control may be improved without additional toxicity. This concept of dose redistribution has already been proven in a randomized phase-III trial for prostate cancer [35].

A group from Brazil performed a phase-I trial of 20 × 2.75 Gy hypofractionated radiotherapy with concurrent cisplatin in advanced stage (75% stage IV) HNSCC and found that the acute toxicity rate was comparable to that of standard radiotherapy with concomitant chemotherapy [26]. Another prospective trial by the Mehanna group also showed that 25 × 2.6 Gy with concurrent chemotherapy resulted in tolerable acute toxicity in locally advanced oropharyngeal carcinoma [24]. From this, we may conclude that hypofractionation for HNSCC is well tolerated, at least in the acute phase and in large volume tumors, with and without the use of a concurrent radiosensitizer. Recently, a subgroup analysis of the PET NECK study was reported to support the use of a hypofractionated regimen during the COVID pandemic [25]. In this trial, 564 patients with locally advanced HNSCC receiving chemoradiotherapy were randomized to a planned neck dissection or active surveillance by FDG-PET. Three radiotherapy fractionation schedules (7, 6 or 4 weeks) were permitted: 56 patients received 20 × 2.75 Gy. There were no significant differences between the three fractionation schemes in terms of locoregional control, overall survival and quality of life after a minimum follow-up of two years.

We performed a planning study of HYDRA dose prescriptions in comparison to conventional fractionation for cT1-4N0-3M0 oropharyngeal (*n* = 4) and hypopharyngeal (*n* = 5) HNSCC patients. For all nine patients, hypofractionated, dose-redistributed radiotherapy allowed for an inhomogeneous boost up to 63 Gy within the macroscopic tumor and a dose reduction in all surrounding organs at risk (OAR) in comparison to standard of care radiotherapy. These results were presented at ECHNO-ICHNO 2021 [36].

With HYDRA, the overall treatment time is four weeks instead of the conventional 6–7 weeks. Patients will therefore receive only four courses of weekly 40 mg/m² cisplatin (160 mg/m² cumulative dose). There are data indicating that a minimal total dose of 200 mg/m² per treatment is associated with improved locoregional control [37]. However, in this setting the cisplatin dose does not lead to a reduction in distant metastasis [38]. From this, we conclude that a minimum dose of 200 mg/m² is not mandatory as a fixed threshold, but can be considered a surrogate of the number of weeks that a patient has received adequate radiosensitization (i.e. at least 5 of 7 weeks in total). We therefore do not consider it necessary to increase the weekly dose of cisplatin in the HYDRA arm, which otherwise may also result in additional toxicity.

By conducting two parallel phase-I trials, it is the aim to prove that HYDRA dose prescriptions are safe, for both proton and photon radiotherapy and for larger tumors. As all HNSCC patients who apply for definitive therapy will directly benefit from a reduced overall treatment time of four weeks instead of seven weeks, this will result in a significant reduction in treatment burden and costs. Actually, the radiobiology models used for this trial and lowered radiation dose prescriptions predict improved tumor control against a reduction of side effects. In the case of favorable safety and efficacy results, this study can subsequently be expanded into a randomized efficacy trial with the ultimate goal of facilitating the clinical implementation of HYDRA as a standard of care. Fewer fractions also imply lower costs, which is highly attractive for the sustainability of healthcare systems, specifically regarding the reimbursement of proton therapy. By longitudinal extensive translational immune monitoring, the objective is to prove that the immune system will be significantly spared by HYDRA. Furthermore, patient- and tumor-specific parameters that contribute to radiation-induced lymphodepletion will be identified. The information gained by these analyses is essential to improve individualized treatment. Actionable immune targets and their temporal patterns will be identified, so they can be tested in future hypofractionated immunotherapy combination trials. In conclusion, this phase I trial is therefore a very important step towards future personalized immune-radiotherapy combinations with the ultimate goal of improving survival for patients with HNSCC.

## Data Availability

Not applicable.

## Abbreviations

CPS: Combined positive score
CTCAE: Common Terminology Criteria for Adverse Events
CTV: clinical target volume
DC: dendritic cel
DLT: dose limiting toxicity
DSMB: Data Safety Monitoring Board
ENI: elective nodal irradiation
GTV: gross tumor volume
HNSCC: head and neck squamous cell carcinoma
HPV: human papillomavirus
HYDRA: HYpofractionated Dose-redistributed RAdiotherapy
IGRT: image guided radiation therapy
IMRT: intensity modulated radiation therapy
MBI: model-based indication
MHC: major histocompatibility complex
NTCP: normal tissue complication probability
OAR: organ at risk
OS: overall survival
PD-L1: programmed death-ligand 1
PFS: progression free survival
PROM: patient-reported outcome measure
PTV: planning target volume
SIB: simultaneous integrated boost
SOC: standard of care
WHO: World Health Organization
